## Abstract

**Background:**

Compensation and adaptation therapies have been developed to improve community functioning via improving neurocognitive abilities in people with schizophrenia. Various modes of delivering compensation and adaptation therapies have been found to be effective. The aim of this trial is to compare two different cognitive interventions, Compensatory Cognitive Training (CCT) and Computerised Interactive Remediation of Cognition–Training for Schizophrenia (CIRCuiTS). The trial also aims to identify if mismatch negativity (MMN) can predict an individual’s response to the compensation and adaptation programmes.

**Methods:**

This study will use a randomised, controlled trial of two cognitive interventions to compare the impact of these programmes on measures of neurocognition and function. One hundred clinically stable patients aged between 18 and 65 years with a diagnosis of a schizophrenia spectrum disorder will be recruited. Participants will be randomised to either the CCT or the CIRCuiTS therapy groups. The outcome measures are neurocognition (BACS), subjective sense of cognitive impairment (SSTICS), social functioning (SFS), and MMN (measured by EEG) in people with schizophrenia spectrum disorders.

**Discussion:**

This trial will determine whether different approaches to addressing the cognitive deficits found in schizophrenia spectrum disorders are of comparable benefit using the outcome measures chosen. This has implications for services where cost and lack of computer technology limit the implementation and dissemination of interventions to address cognitive impairment in routine practice. The trial will contribute to the emerging evidence of MMN as a predictor of response to cognitive interventions.

**Trial registration:**

Australian New Zealand Clinical Trials Registry (ANZCTR) ACTRN12618000161224. Registered on 2 February 2018. Protocol version: 4.0, 18 June 2018.

## Introduction

### Background and rationale

Functional deficits (i.e. social skills, community functioning) are a core feature of schizophrenia. They represent key diagnostic criteria for the disorder that precede illness onset and are a strong predictor of outcome. These deficits do not respond to current psychopharmacology [1–3], thus underscoring the need to develop alternative interventions such as psychosocial treatments to address functional impairments.

Over the last 15 years, there has been renewed awareness of the impact of cognitive impairment in schizophrenia and the effect these deficits have on recovery and treatment outcomes [4, 5]. Compensation and adaptation therapies have been defined as “behavioural training-based intervention that aims to improve cognitive processes (attention, memory, executive functioning, social cognition or meta cognition with the goal of durability and generalisation)” [6]. A meta-analysis published in 2011 demonstrated that compensation and adaptation therapies had an overall effect size of 0.45 on global cognition with larger effect when combined with adjunctive rehabilitation (ES = 0.59) [6].

The research to date has not been able to refine who responds to cognitive compensation and adaptation therapies. There is interest in objective tests such as electroencephalography (EEG). EEG findings of attenuation in mismatch negativity (MMN) in auditory oddball tasks are one of the most robust and replicable neurophysiological markers of schizophrenia [7]. The MMN response occurs when a rare, unexpected sound is played in a repetitive sequence of sounds and is thought to reflect a brain response to an error in what is predicted. This sensory prediction error response has also been shown to relate to functional ability in people at risk for schizophrenia [8]. There are pilot studies indicating it may be able to predict and be an objective indicator of people who would benefit from psychosocial interventions [9–11]. Being able to have more precise information on who would respond to interventions, especially psychosocial interventions that require a weekly commitment over months, would benefit participants and not expose people to the potentially demoralising effect of attending a therapy that they were not able to benefit from [12].

Many cognitive remediation programmes are delivered via computer-based programmes often accessed online [6]. The cost of the infrastructure requirements of these programmes can pose a barrier to their implementation in some services. Pen and paper programmes to address cognitive deficits have been previously developed and evaluated [6]. This study is aimed at comparing a pen and paper cognitive adaption programme (CCT) [13–15] with a computer-based cognitive remediation programme, CIRCuiTS [16].

### Objectives

This study will use a randomised controlled trial to test the equivalence of CCT compared with CIRCuiTs to address the cognitive deficits of schizophrenia spectrum disorders. The primary objective is to examine the equivalence of CCT in improving neurocognitive deficits in people with schizophrenia spectrum disorders compared with CIRCuiTS. The secondary objective examines if CCT and/or CIRCuiTS are associated with objective and subjective improvement in community and cognitive functioning. In addition, we aim to determine whether MMN at baseline can be used to predict on an individual level, who might benefit from either treatment.

### Trial design

The design is a single-blind, randomised controlled trial to examine the equivalence of CCT and CIRCuiTS. The trial also aims to examine if MMN at baseline can predict response to the compensation and adaptation therapies and if MMN improves from baseline to post-treatment.

The study will include 100 clinically stable patients with a schizophrenia spectrum disorder. Participants will be randomised in a 1:1 ratio to join either the CCT group or the CIRCuiTS group. Participants will all be active cases in Metro South Addiction and Mental Health Services (community based). Participants in the study will continue to receive standard clinical care (i.e. there are no restrictions on medication or psychosocial interventions, apart from participants receiving therapies addressing neurocognition). These two interventions will be delivered by trained mental health staff once (CCT 2-h session) or twice (CIRCuiTS 1-h sessions) per week for 12 weeks. Groups will be based on a maximum of 6 participants per facilitator. Individual clinical assessments will be at baseline, at post-treatment, and at 3-month follow-up. Randomisation will be carried out using a computer-generated randomisation table.

## Method: participants, interventions, and outcomes

### Study setting

The study will be conducted in the Community Mental Health Centres within Metro South Addiction and Mental Health Services, Queensland, Australia.

### Eligibility criteria

The specified inclusion criteria are as follows: (1) aged between 18 and 65 years (inclusive), (2) fulfilling the clinical diagnosis of DSM-V criteria for schizophrenia spectrum disorder, (3) absence of uncorrected sensory impairments, (4) English literacy skills greater than grade 4 as per years of education, and (5) agreement to participate, with capacity to consent and able to follow the study instructions and procedures.

The specific exclusion criteria are as follows: (1) presence of substance dependence (with the exception of tobacco), (2) intellectual handicap (estimated using the Test of Premorbid Functioning (TOPF)), (3) people who are unable to understand or communicate in English or with English literacy skills less than grade 4 as per years of education, and (4) comorbid physical illnesses that would impair the participants’ ability to complete the trial.

### Compensatory Cognitive Training

CCT is a 2-h ×12 session manualised cognitive compensatory training programme that focusses on the use of strategies to improve real-world cognitive functioning. The manual covers exercises in prospective memory, attention, memory, and executive functioning. There are some drill and practice of tasks, but the emphasis is on strategy use and incorporation into everyday activities. CCT is delivered through paper and pen tasks.

### CIRCuiTs

CIRCuiTS (Computerised Interactive Remediation of Cognition–Training for Schizophrenia) is a modular package including tasks of a wide range of cognitive functions (particularly executive function and memory), intended to allow therapy programmes to be flexibly designed to incorporate only relevant tasks. Prior to attempting a task, the participant needs to register how long they believe the task will take, how difficult the task is expected to be, and the strategy they intend to use. They receive computer feedback on these dimensions and re-rate how useful the strategies were with the goal of developing metacognitive knowledge and awareness. CIRCuiTS is run for 1 h twice a week and is delivered through a computer. The CIRCuiTS programme used consists of 40 stages. The tasks are progressively more difficult as the participant works through the programme. Twenty sessions are considered an adequate treatment exposure.

### Outcomes

A battery of validated clinical measures will be conducted at baseline, at post-treatment, and at 3-month follow-up. Raters who are blind to the randomisation of condition (registered psychologists) will complete the measures. The assessors instruct the participant not to reveal their group allocation.

The following measures will be used:
Brief Assessment of Cognition in Schizophrenia (BACS) [17] is an instrument that assesses the aspects of cognition found to be most impaired and most strongly correlated with outcome in patients with schizophrenia. This is the primary outcome measure.Test of Premorbid Functioning (TOPF) [18] is a test of premorbid intelligence as estimated from reading ability.Subjective Scale to Investigate Cognition in Schizophrenia (SSTICS) [19]. This measures the perception of cognitive abilities when completing everyday tasks.Social Functioning Scale (SFS) [20] assesses areas of functioning that are crucial to the community maintenance of individuals with schizophrenia.Brief Psychiatric Rating Scale (BPRS) [21] is a widely used scale for measuring symptom severity of patients with schizophrenia.Electroencephalography (EEG). Participants will listen to a duration auditory oddball paradigm while their brain responses are measured with EEG. An auditory oddball paradigm consists of presentations of sequences of predictable sound stimuli (standard sounds) that are infrequently interrupted by unpredictable sound stimuli (deviant sounds). Sounds will be delivered via headphones and will vary in duration. All tones will be presented in a sound range that is comfortable for the participants. In the “volatility” auditory oddball task, the participants will be asked to pay attention to the sounds in order to judge the proportion of different sound types and rate their confidence on this judgement. This will allow us to assess the ability of participants to learn the statistical relationships of sound types, as well as the confidence on their own judgement. Prior to the experiment, the participants will be familiarised with the different sound types and trained with two short practice tasks. Participants will make responses using a computer keyboard and a mouse. The duration of the practice task will be 2 min, and the duration of the volatility auditory oddball task will be approximately 18 min, with a total duration of testing of approximately 20 min per participant, including breaks.

The TOPF, SSTICS, BPRS, and EEG are secondary outcome measures.

### Participant timeline

The study will include clinically stable patients, living in the community with a diagnosis of a schizophrenia spectrum disorder receiving community-based clinical care in Metro South Addiction and Mental Health Services. These two interventions will be delivered by trained and experienced mental health staff once or twice per week for 12 weeks. Groups will be based on two to six participants per group. Individual clinical assessments will be at baseline, post-intervention, and 3-month follow-up (see Fig. 1).

**Fig. 1 Fig1:**
[figure not shown]
Schedule of enrolment, intervention, and assessment

### Sample size

In this equivalence study, we will focus on the primary outcome of cognition. We based our power analysis specifically on the BACS. We estimate a dropout rate of 15–20% (from treatment to 3-month follow-up) resulting in a final sample size of approximately 80 participants who will complete the study. This estimate is based on the dropout rates for studies with participants with serious mental illness as well as our experience with group randomised controlled trial research. Due to practicalities of group size and opportunities for running groups over the study timeframe, the maximum number of participants was set at one hundred.

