## Methods: data collection, management, and analysis

### Data collection and statistical methods

The primary efficacy analysis will assess average treatment group differences for the primary outcome measure BACS, over the entire study period (baseline, post-intervention, follow-up), and will use a likelihood based mixed-effects model, repeated measures (MMRM) approach. The MMRM model includes the fixed, categorical effects of treatment (CCT or CIRCuiTS), visit (baseline, 12 and 24 weeks), and treatment-by-visit interaction, as well as the continuous, fixed covariates of baseline score and baseline score-by-visit interaction. The MMRM includes all available data at each time point and is the preferred method of analysing clinical trial data in psychiatry as compared to more traditional repeated measures analysis of variance (ANOVA) and analysis of covariance (ANCOVA) models. Planned comparisons will be done with the MMRM models to determine between-group differences in change of symptoms measures from baseline to weeks 12 and 24. Results from the analysis of dichotomous data will be presented as proportions, with 95% confidence interval, and Fisher’s exact *p* value where appropriate. Non-parametric statistics will be used when assumptions for parametric methods are violated. Effect sizes will be calculated using Cohen’s guidelines. All tests of treatment effects will be conducted using a two-sided alpha level of 0.05 and 95% confidence intervals.

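### The sample size section invokes a BACS power analysis for equivalence, but the only reason given for 100 is feasibility, and about 80 completers support only fairly wide margins

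*Protocol article*

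**What the plan says.** The Objectives section states: "The primary objective is to examine the equivalence of CCT in improving neurocognitive deficits in people with schizophrenia spectrum disorders compared with CIRCuiTS". The Sample size section calls the trial an equivalence study and says "We based our power analysis specifically on the BACS". It gives a dropout range of 15–20%, "resulting in a final sample size of approximately 80 participants who will complete the study". It then explains where the number came from: "Due to practicalities of group size and opportunities for running groups over the study timeframe, the maximum number of participants was set at one hundred". No power figure or required number accompanies the mention of a power analysis.

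Under Data collection and statistical methods, the primary analysis is a mixed model for average group differences on the BACS over the study period, adjusted for baseline, with planned comparisons at weeks 12 and 24. The error rate is set by: "All tests of treatment effects will be conducted using a two-sided alpha level of 0.05 and 95% confidence intervals".

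The one effect size for cognition that bears on the question is in Background and rationale, where a meta-analysis is reported to show that "compensation and adaptation therapies had an overall effect size of 0.45 on global cognition". The article does not use it as a margin or as a sample-size input.

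**The concern.** The Sample size section points to a statistical basis and then gives a practical one. A reader who stops at the power sentence will assume that 100 recruits, or 80 completers, were shown to be enough for an equivalence conclusion on the BACS. Nothing in the section links a power result to either number.

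This matters because the analysis described is a two-sided test of difference. In a trial labelled as equivalence and said to rest on a power analysis, a non-significant difference is easily read as proof that the two programmes work equally well. The article's Discussion in the abstract already looks ahead to implications for services that lack computers. If the interval at 80 completers is wide compared with the benefit these therapies are thought to give, that reading could hide a substantial loss of benefit in either arm.

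**Working it through.** **The plan's own figure.** 100 × (1 − 0.20) = 80, and 100 × (1 − 0.15) = 85. So about 80 is the 20% end of the stated dropout range applied to the cap. It follows from the cap, not from a power calculation. The power analysis cannot be reproduced, because the article gives no margin, SD, target power or correlation.

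**Inputs from the article.** About 80 completers; 1:1 allocation, so 40 per arm; 95% confidence intervals; adjustment for baseline; visits at baseline, 12 and 24 weeks.

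**Assumptions.** SD = 1 (results in SD units); true difference zero; 80% power; baseline correlation r from 0 to 0.9; no clustering. For the averaged contrast I assume compound symmetry, with the same r between all visits.

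**Formulas.**
- SE = √(2/40 × V).
- Single visit: V = 1 − r².
- Average of the two post-baseline visits: V = (1 + r)/2 − r².
- Half-width of the 95% interval = 1.96 × SE.
- Power for margin m = 2Φ(m/SE − 1.96) − 1, floored at zero.
- Smallest margin with 80% power = (1.960 + 1.282) × SE.

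Example, r = 0, single visit: SE = √0.05 = 0.2236; half-width 1.96 × 0.2236 = 0.438; margin 3.242 × 0.2236 = 0.725. Example, r = 0.8, averaged: V = 0.90 − 0.64 = 0.26; SE = √0.013 = 0.114; half-width 0.223; margin 0.370.

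**Results with the 95% interval.**

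| r | Contrast | Half-width (SD) | Margin at 80% power (SD) | Power, m = 0.45 | Power, m = 0.225 |
|---|---|---|---|---|---|
| 0 | single visit | 0.438 | 0.725 | 4% | 0% |
| 0.5 | single visit | 0.380 | 0.628 | 28% | 0% |
| 0.7 | single visit | 0.313 | 0.518 | 61% | 0% |
| 0.8 | single visit | 0.263 | 0.435 | 84% | 0% |
| 0.9 | single visit | 0.191 | 0.316 | 99% | 27% |
| 0 | average | 0.310 | 0.513 | 62% | 0% |
| 0.5 | average | 0.310 | 0.513 | 62% | 0% |
| 0.7 | average | 0.263 | 0.435 | 84% | 0% |
| 0.8 | average | 0.223 | 0.370 | 95% | 1% |
| 0.9 | average | 0.164 | 0.271 | >99% | 53% |

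The averaged margin does not fall steadily with r. V peaks at r = 0.25 (0.5625), where the margin is 0.544 SD, so 0.513 to 0.370 describes the ends of the range 0 to 0.8, not its maximum.

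**Sensitivity.**
- With a 90% interval (two one-sided 5% tests), the single-visit margins are 0.654 (r = 0), 0.467 (0.7) and 0.393 (0.8).
- Half the cited effect is 0.45/2 = 0.225 SD. The most favourable case tried was r = 0.9, averaged visits and a 90% interval, which gives 70% power.
- With 85 completers every margin shrinks by the factor √(40/42.5) = 0.970, about 3%.
- Therapy is given in groups of two to six. An assumed design effect of 1.2 widens every margin by √1.2 = 1.095, about 10%.
- A t-based simulation of 20,000 runs for single-visit cases agreed with the normal approximation within about 2 percentage points.

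**The case against.** The best defence has four parts.

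First, a power analysis and a feasibility cap can coexist. The article does not say that 100 came from the power analysis, and it discloses the practical reason. The details may be in the full protocol. This stands to the extent that a reader might infer that no power analysis was done, or that the missing inputs are themselves the fault; the article supports neither. What remains is that the section invokes a power analysis in support of the size and then gives only a non-statistical reason for the number.

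Second, a reader might infer that 80 completers cannot show equivalence within any useful margin. The article does not support that. It names no margin, SD or correlation, so what counts as useful is a judgement. At r = 0.8, power for a 0.45 SD margin is 84% at a single visit and 95% for the averaged contrast. An 80%-power margin is also not a limit on what an observed interval can show: a half-width of 0.26 SD could fall inside a margin of 0.30 SD.

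Third, the primary analysis is described as an average over the study period, so single-visit figures alone would understate its precision. This is right, and both contrasts are shown. The single-visit figures apply to the planned comparisons at weeks 12 and 24.

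Fourth, the mixed model uses all available data, so participants lost after week 12 still contribute, and dropout may be nearer 15%. Both would help a little (about 3% for 85 completers). Clustering by therapy group works in the other direction.

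**Conclusion.** The point holds in a conditional form. The article implies a power basis for an equivalence conclusion, but the only stated origin of 100 is feasibility, and about 80 is that number less 20%.

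Under the assumptions listed and with r between 0 and 0.8, the smallest margin with 80% power is about 0.73 to 0.44 SD at a single visit (0.725 and 0.435 before rounding up). For the average of the two post-baseline visits it is about 0.51 SD at r = 0 and 0.37 SD at r = 0.8, with a peak of about 0.54 SD near r = 0.25. All of these are before clustering. Set beside a cited total effect of 0.45 SD, margins of this size could allow much or all of the class benefit to be lost while equivalence is declared. A margin of half that effect does not reach 80% power in any scenario tried up to r = 0.9.

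The conclusion depends on assumed correlations and on using 0.45 SD only as a yardstick. It does not show that the trial must fail. It shows that the power sentence should not be relied on, and that a non-significant difference would not establish equivalence.

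**What to change.** In the Sample size section, state that the number was set by feasibility. If a power analysis was done, report its inputs and result there or cite the document that holds them.

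Prespecify and justify a BACS equivalence margin, or cite it if it already exists in the full protocol or analysis plan. For the stated primary contrast, report the expected interval half-width and the power at about 80 completers, showing the SD, correlation and clustering assumptions as assumptions rather than as expected results.

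In the statistical methods section, add the decision rule: equivalence is claimed only if the confidence interval lies wholly within the margin. Otherwise the estimate and interval are reported without an equivalence claim, and a non-significant difference is not read as equivalence.

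This needs a wording amendment and agreement on a margin before unblinded data are seen. No extra patients are needed. The price is that the trial's stated strength becomes less favourable.

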### Recruitment

Participants will be recruited through the public mental health community clinics. Participants will continue to receive standard clinical care for the duration of the study. Medication prescribed at baseline will be collected and any changes noted. Participants will not be compensated for their time spent in treatment or assessment sessions.

## Methods: assignment of interventions

### Allocation and blinding

A minimum of twelve participants will be recruited for each round of the study. Participants will be recruited and randomly allocated in block sizes of four using randomisation procedure Statistical Analysis System (SAS) 9.4 by a member of the research team not involved in the delivery of the intervention or outcome assessment. As participants may drop out of therapy, the group numbers may fall to no lower than two participants. The therapeutic group size is two to six participants. Information about the treatment allocation will be emailed to the therapists who will contact participants about their therapy.

A battery of validated clinical measures will be conducted by trained research assistants, who are blind to group membership, at baseline, post-intervention, and 3-month follow-up. The research staff who undertake the outcome assessments will be blind to group allocation and will advise participants not to reveal their treatment. If a patient reveals this information, this will be noted for post hoc analyses of the data.

